## Abstract

**Background:**

Chronic obstructive pulmonary disease (COPD) remains a major health problem, strongly related to smoking. Despite the publication of practice guidelines on prevention and treatment, not all patients with the disease receive the recommended healthcare, particularly with regard to smoking cessation advice where applicable. We have developed a tailored implementation strategy for enhancing general practitioners’ adherence to the disease management guidelines. The primary aim of the study is to evaluate the effects of this tailored implementation intervention on general practitioners’ adherence to guidelines.

**Methods/Design:**

A pragmatic two-arm cluster randomized trial has been planned to compare care following the implementation of tailored interventions of four recommendations in COPD patients against usual care. The study will involve 18 general practices (9 in the intervention group and 9 in the control group) in Poland, each with at least 80 identified (at the baseline) patients with diagnosed COPD. The nine control practices will provide usual care without any interventions. Tailored interventions to implement four recommendations will be delivered in the remaining nine practices. At follow-up after nine months, data will be collected for all 18 general practices. The primary outcome measure is physicians’ adherence to all four recommendations: brief anti-smoking advice, dyspnea assessment, care checklist utilization and demonstration to patients of correct inhaler use. This measurement will be based on data extracted from identified patients’ records. Additionally, we will survey and interview patients with chronic obstructive pulmonary disease about the process of care.

**Discussion:**

The results of this trial will be directly applicable to primary care in Poland and add to the growing body of evidence on interventions to improve chronic illness care.

**Trial registration:**

This trial has been registered with Clinical Trials Protocol Registration System. Trial number: NCT01893476.

## Background

Chronic obstructive pulmonary disease (COPD) remains a major health problem. Worldwide it has been ranked as the sixth leading cause of death for both genders [1]. In 2020 COPD is projected to rank fifth worldwide in burden of disease. It is also projected to be the fourth leading cause of death worldwide by 2030 due to an increase in smoking rates and demographic changes in many countries [2]. A national survey conducted in Poland in 2007 indicated that 34% of men smoked daily, 2% were occasional smokers, 19% were former smokers and 45% had never smoked. In women these percentages were 23, 3, 10 and 64% respectively [3].

Epidemiological studies of COPD on a representative sample have not been performed in Poland, but estimates from smaller studies suggested a relatively high prevalence. Studies in selected geographical areas found that signs and symptoms of COPD were seen in about 10% of patients over 40-years old [4]. Studies in large cities in Poland showed a 9.8% prevalence of COPD in populations between 41 and 72 years old [5]. These data are similar to other European data, describing prevalence rates of 4 to 11% in adults in Europe [6]. The total number of people suffering from COPD in Poland is estimated to be about 2 million (on a population of 38 million inhabitants). This places COPD as the third most frequent chronic illness, and it is the fourth most common cause of death in Poland [7].

In Poland, most COPD patients are treated in primary care, which is the entry point to the public health care system. The system is based on compulsory health insurance, managed by the National Health Fund (NHF), which purchases health services from physicians and health care enterprises. Patients register with a particular primary care practice, signing on to an individual general practitioner’s list of patients, and can be referred for specialist out-patient consultation or to a hospital, if needed. Ambulatory care (primary and out-patient specialist services) is provided by therapeutic entities (clinics or dispensaries) and by medical practices. Rehabilitation and long-term care are provided within both the health care sector and the social care sector, but coordination between the two is poor. Furthermore, limited financial resources available to the NHF and shortages of medical personnel have negative effects on access to health care services [8].

There is no national consensus on the care paths for COPD, and various guidelines on COPD are used, some of which national and some international [9,10]. However, the guidelines in use share most of recommendations that we have identified and prioritized for the purpose of this trial. There is very little evidence on the degree of adherence to the guidelines for the management of COPD used by Polish physicians. One study, which evaluated the NHF funded COPD prevention program aiming to reduce the incidence and disability related to COPD by complex educational, diagnostic and therapeutic interventions in people at risk, showed low rates of participation of primary health care providers despite additional funding. An interesting finding was that the extent of program completion was strongest for qualified general practitioners compared to physicians without specialty training or non-generalists: internal diseases specialists and pediatricians working at primary care setting [11].

It is unclear whether studies on the implementation of evidence-based recommendations for primary care in COPD patients from countries with well-developed primary care systems, like the United Kingdom and the Netherlands [12,13] can be translated to Poland. In searching the Polish medical literature, we did not find published research on the implementation of COPD guidelines or recommendations in Poland. The authors identified three papers with results partially related to the subject of this study [14-16]. These found that 30% of patients with the diagnosis do not fulfill criteria for COPD, in 15% of cases spirometry had not been performed, and more than 70% of patients received inhaled steroids. Such findings suggest that adherence to diagnostic and management recommendations are inadequate.

Preliminary qualitative evidence from the authors’ earlier work showed that not one single guideline for COPD was used by all GPs or medical specialists. However, responders pointed out the individual recommendations most commonly used and the barriers to their implementation. The identified barriers for adhering to specific recommendations were: (1) lack of knowledge on smoking cessation brief intervention, (2) dyspnea evaluation tool was unavailable, (3) lack of a care plan, and (4) lack of demonstration-inhaling devices. Other research has indicated that the treatment parameters from the (COPD) guidelines are not always measured [17-19]. The consequence is that not all patients receive recommended advice and treatment from their physicians.

This study is part of the Tailored Implementation for Chronic Diseases (TICD) international collaborative research project, which is being undertaken in Germany, Norway, Poland, the Netherlands and the United Kingdom. The aim is to develop and test methods of tailoring knowledge-implementation interventions to determinants of practice in chronic illness care [20]. In Poland, the focus is on the implementation of COPD guidelines in primary care. The research group in Poland selected four key recommendations applicable to primary care (Table 1) from the four COPD guidelines most relevant to primary care and used in Poland.

**Table 1 T1:** Key recommendations for COPD management

A	Brief smoking cessation counseling is effective and every tobacco user should be offered stop-smoking advice at every contact with health care providers.
B	The prognosis of COPD should be estimated using the mMRC dyspnea scale.
C	The patient should be given the basic information about his/her disease, its treatment and the expected effects of applied drugs, in order to enhance that the patient takes an active, participating role in the long-term treatment.
D	The patient should be trained in the correct use of all devices which he/she will use for inhalation.

### Objective

The objective of this study is to examine the effectiveness of a tailored implementation strategy for enhancing physicians’ adherence to four recommendations for the management of COPD patients in primary care. The process of tailoring implementation interventions and the impact on the effectiveness of the strategy will also be studied.

### Research questions

The questions we will be attempting to address in this study are as follows: what is the effectiveness of a tailored implementation strategy compared to usual care in enhancing primary care physicians’ adherence to guidelines?, and how do the determinants of practice targeted by the tailored implementation strategy change over time, and how does their variability relate to the effectiveness of implementation strategies?

## Methods/design

### Study design

This study is a two-arm pragmatic, cluster randomized trial (CRCT) [21,22], which compares a tailored intervention program directed at general practitioners with usual primary care. It is localized in Lodz, the third largest city in Poland, with a population of about 750.000 inhabitants with broadly average mortality and morbidity, although specific health data are lacking. It aims to include general practices with adult patients with COPD under their care. The general practices will be randomized into two equally sized groups

### Sample size calculation

The sample size calculation indicated that, for a two-arm cluster controlled randomized trial, a minimum number of 16 primary care practices with minimum of 30 COPD patients per practice is required. A total of 16 clusters and at least 480 subjects is required at baseline and follow-up (8 clusters in each study arm) to detect a difference, or change in adherence, of between 40% and 60% with selected COPD recommendations, between the intervention group (facilitating adherence to guidelines) and the control group without intervention (usual care), with 80% power, a two-tailed alpha of 0.05, and intra-cluster correlation of 0.05.

A standard sample size formula was used to calculate the initial unadjusted sample size requirements, followed by appropriate adjustment for clustering by general practice according to Campbell *et al.*[23], with expected small clustering effect (ICC = 0.05). Previous reported ICCs vary from 0.03 for smoking advice [23] to 0.05 for cluster randomized trials in primary care (data from Trial of Older People in the Community) [24,25]. It was decided to increase the sample by 10% to account for contingencies such as non-response or recording error, giving a total of 18 practices.

With regard to the number of patients with COPD per practice, an assumed response rate of 58% [26,27] and a dropout of 35% [28], which led to a total of 80 COPD patients needed per general practice at baseline. Patients will be selected via the medical records using ICD code J44, and medical records will be labelled at the baseline of the study.

### Setting and participants

#### General practices

Eighteen general practices selected with random sampling within the Lodz region of Poland, with 80 or more registered COPD patients each (identified via J44 ICD-10), will be invited to participate in the study. The baseline number of COPD patients is determined by assumed response rate and dropout described above, to assure at least 30 at follow-up. Some of the practices were previously involved in other studies and have an established agreement with the Medical University of Lodz in the field of research and vocational training. The main study has been planned to take place between December 2013 and September 2014. After having given informed consent, primary care practices will be randomly allocated to one of two groups. The medical records of patients with COPD will be labelled with blue stickers at the baseline of the study (Figure 1).

**Figure 1 F1:**
[figure not shown]
Flowchart for CRCT.

#### General practitioners

All GPs working in targeted practices are required to participate in the study.

### Eligibility criteria

#### Patients

Eligible patients will be approached at follow-up. Only patients who were treated in the same practice at baseline (with the labelled medical records) will be considered for inclusion so that the study is prospective. Exclusion criteria are: (1) terminal illness and (2) cognitive impairments. At follow up 80 patients, randomly selected (with personal data unknown to researchers) will receive an informed consent form and an invitational letter via their GPs, and will be asked to fill in a questionnaire and/or participate in an audio taped interview or focus group. This letter will provide comprehensive information about the study. Contact details of the researchers will be provided so that patients can ask questions. Patients’ information gathered from questionnaires or from interviews will be anonymized.

### Randomization

Randomization will be performed by a statistician not involved in the trial, through a computer. The general practices will be allocated randomly to two equally sized groups: an intervention group and a control group. At the end of the study a group of patients will be randomly selected in order to invite them to fill out the end-of-study questionnaire. Participants in this trial will not be blinded. Descriptive statistics and logistic regression will be used for analyzing the data. The level of statistical significance will be *p* < 0.05.

### Blinding

COPD patients within each participating intervention and control practice will be identified at the baseline. Because of the nature of the intervention, it is not possible to blind GP participants (in practices).

Outcome assessment will not be blinded as the research assistants will be aware of practice group allocation, and the data analysis will be performed by researchers and a statistician blinded to the study group.

### Implementation program

The implementation program is based on multiphase research performed in the TICD project. In the first phase has identified barriers and enablers for improving COPD care, focusing on the four recommendations selected. One hundred and sixty determinants were listed, grouped (according to the TICD checklist domains [29]), and judged by our research team on importance and changeability using Likert scales. The result was 24 determinants of practice. The second phase of the project, identified determinants were prioritized during focus group discussions and matched to implementation strategies. The final decisions on the interventions matched to the determinants for four recommendations are presented in Table 2. This procedure led to the following implementation program.

**Table 2 T2:** Identified determinants and interventions for selected recommendations

	**Recommendation**	**Determinant**	**Proposed intervention(s)**
A	A brief clinician’s counseling to quit smoking	Additional training for GPs	Labeling medical records for COPD patients and training GPs in brief intervention
B	The prognosis of COPD should be estimated using mMRC dyspnea scale	Prepared form	Additional form (in paper or in computer medical records) with mMRC scale
C	The patient should be given the basic information about his/her disease	Checklist in medical history	Providing physicians with a checklist in patients’ records to facilitate what should be done during consultation
D	The patient has to be trained in the correct use of all devices	Inhaling devices for training	To provide GPs’ clinics with training inhaler devices to show patient’s how to use them

#### Smoker identification and brief intervention

First, participating physicians will receive training in brief smoking status identification and anti-smoking counselling, and will be asked to record information about the actions they perform in patients’ medical records. This intervention will address the recommendation of Global Initiative for Chronic Obstructive Lung Disease (GOLD) based on Wilson et al. [30].

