#### Dyspnea evaluation

Second, an additional form containing the modified Medical Research Council Dyspnea Scale (mMRC) will be inserted into patients’ medical records on paper. It is a validated patient symptom questionnaire for a subjective assessment of COPD symptoms. This intervention will address the recommendation of National Institute for Health and Care Excellence based on Fletcher et al. [31].

GPs will be asked to determine the patient’s status according to the scale and put this information into the patient’s medical records.

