#### COPD check list

Third, a checklist for practitioners will be provided with information about what should be done while consulting on a patient with COPD. This intervention will address the recommendation of the European Respiratory Society [32]. It will cover points such as that a patient should be given basic information about COPD, its treatment, and the expected effects of applied drugs, making the patient an active, aware participant in their long-term treatment. GPs will be asked to provide patients with the information and tick a box if it is done.

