#### Demonstration inhaler devices

Finally, practices will be provided with training inhaler device sets for health care staff and train GPs on how to instruct patients to use devices properly. This intervention will address the recommendation of the Polish Society of Lung Diseases [33].

GPs will be asked to teach patients in the correct use of each device and record information about the fact in patient’s medical records.

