### Outcomes/measures

#### Primary outcome

The primary outcome will be the GPs’ adherence to the recommendations, which is dichotomized as follows. A positive score is given if all recommendations are followed, while following less than four recommendations is given a negative score. Data listed in Table 3 will be obtained from the patients’ medical records (independent of the checklist that is provided as part of the intervention) and during interviews. All identified COPD patients who gave informed consent in each practice will be included, and full data protection procedures will be followed.

**Table 3 T3:** Information recorded in patients’ records to determine adherence of a GP the recommendations

1.	Brief anti-smoking counselling performed
2.	Dyspnea assessed
3.	Management process of COPD assessed
4.	Training patient on correct use of inhaling device performed.

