### Data collection

At the end of the study data will be collected by review of medical records of COPD patients identified at the baseline who visited their GPs during the last nine months. Extracted information will cover the following: brief anti-smoking advice performed, information about dyspnea, COPD checklist utilization and training on using inhalers.

Patients with COPD who have given signed informed consent will be asked to fill in a questionnaire and participate in an interview containing questions about the process of care, information received from GPs and patients’ health status perception.

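### Only intervention GPs are asked to record the four actions, and the primary outcome is read mainly from records, so better recording alone can produce a difference in favour of the intervention

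*Protocol article*

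**What the plan says.** All references are to the protocol article.

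**Intervention arm.** Each of the four components carries a request to make an entry:
- Smoker identification and brief intervention: GPs "will be asked to record information about the actions they perform" in the record.
- Dyspnea evaluation: a paper mMRC form is inserted in the record, and "GPs will be asked to determine the patient’s status according to the scale and put this information into the patient’s medical records".
- COPD check list: "GPs will be asked to provide patients with the information and tick a box if it is done".
- Demonstration inhaler devices: "GPs will be asked to teach patients in the correct use of each device and record information about the fact" in the record.

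**Control arm.** The Control group section gives usual care, with feedback only after the study ends.

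**Outcome.** Under Primary outcome, a patient counts as positive only if all four recommendations were followed, and the title of Table 3 describes the items as information found in patients' records. The abstract says "This measurement will be based on data extracted from identified" patients' records. Primary outcome says the data are independent of the intervention's checklist, and it adds a second source: "and during interviews". The abstract and Data collection nevertheless list use of the checklist among the items measured. Data collection also has consenting patients "participate in an interview containing questions about the process of care, information received from GPs".

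**Blinding.** Outcome assessors know the allocation; the data analysts do not.

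**The concern.** The Objective and Research questions concern whether GPs follow the recommendations. The measurement mostly shows whether they wrote down that they did, and the intervention itself changes what gets written down. A control GP who counsels a smoker or demonstrates an inhaler without noting it scores as non-adherent. An intervention GP giving the same care has been asked to note it and, for two of the items, has been handed a form or tick box for doing so.

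The bias runs in one direction, and the all-four rule makes the score sensitive to it because one missing entry turns a positive patient negative. Unblinded extraction does nothing to offset it. What is at stake is the conclusion: the Discussion says an effective programme would warrant wide-scale application, and a recording effect would not justify that.

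**Working it through.** **1. The plan's own figure.** Inputs from Sample size calculation: 40% versus 60%, 80% power, two-sided alpha 0.05, ICC 0.05, 30 patients per practice.
- Unadjusted n per arm = [1.96·√(2·0.5·0.5) + 0.842·√(0.4·0.6 + 0.6·0.4)]² / 0.20² = 96.9, so 97.
- Design effect = 1 + (30 − 1)·0.05 = 2.45. Then 97·2.45 = 237.65 per arm, and 237.65/30 = 7.92, so 8 practices per arm, 16 practices and 480 patients.
- 16·1.10 = 17.6, so 18 practices. 30/(0.58·0.65) = 79.6, so 80 patients per practice.

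The stated sample size reproduces and is not in dispute.

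**2. Which items carry a recording request.**

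| Item | Request, intervention arm | Request, control arm | Removed by the checklist clause? |
|---|---|---|---|
| Smoking advice | note in record | none | no |
| Dyspnea | form, entry in record | none | no |
| Patient information | tick box | none | yes under Primary outcome; no under the abstract and Data collection |
| Inhaler training | note in record | none | no |

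Item 3 is also named in different ways: giving basic information (Table 1), assessing the management process (Table 3), and using the checklist (abstract, Data collection). The trial supplies the checklist only to intervention practices.

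**3. How large a pure recording effect could be.** Let P be the true all-four rate, equal in both arms, and r the probability that a performed action is recorded. The documents give neither, so both are assumptions.
- Items recorded independently: recorded rate = P·r⁴.
- Recording fully correlated (all four noted or none): recorded rate = P·r.
- With 9 practices of 30 per arm, effective n per arm = 270/2.45 = 110.2. SE = √{[p₁(1 − p₁) + p₂(1 − p₂)]/110.2}. The chance of significance comes from a noncentral t with 16 df and noncentrality (p₂ − p₁)/SE.

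Worked line, P = 40%, r = 80% (control) versus 95% (intervention), independent: 0.4·0.8⁴ = 0.164 and 0.4·0.95⁴ = 0.326, odds ratio 2.47. SE = 0.0569, noncentrality = 0.162/0.0569 = 2.85, chance 0.76. Fully correlated: 0.32 versus 0.38, SE = 0.0641, noncentrality 0.94, chance 0.14.

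| P | r, control vs intervention | Independent: recorded rates | Chance significant | Correlated: recorded rates | Chance significant |
|---|---|---|---|---|---|
| 40% | 80% vs 95% | 16.4% vs 32.6% | 76% | 32% vs 38% | 14% |
| 40% | 90% vs 95% | 26.2% vs 32.6% | 16% | 36% vs 38% | 6% |
| 20% | 80% vs 95% | 8.2% vs 16.3% | 41% | 16% vs 19% | 9% |
| 20% | 90% vs 95% | 13.1% vs 16.3% | 10% | 18% vs 19% | 5% |

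Without a recording difference the chance would be 5%.

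**The case against.** The plan does contain a safeguard. Primary outcome sets the intervention checklist aside and names interviews as a further source. A reader might therefore answer that the outcome is not simply a count of prompted entries. Part of this stands. For item 3 the tick box is the only recording request described, and under that clause it would not be scored. Nor does the abstract say that records are the only source, so it would go too far to claim that patient reports play no part in the primary outcome. How they would be combined with the records may be set out in the full protocol or analysis plan.

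The safeguard does not settle the matter. As described, the checklist serves one item of four, and two other parts of the article count its use. Interviews reach only patients who consent.

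A second fair objection is that the 76% is fragile. It needs independent recording of the four items, whereas a GP may keep full notes or none. It would be wrong to state as fact that the all-four rule raises recording completeness to the fourth power; that holds only under independence. The correlated column is the other extreme, and the truth probably lies between the two.

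A reader might also infer that a positive result would be an artefact of documentation. The documents do not support that: they contain no recording rates and show only that recording alone can produce a difference.

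**Conclusion.** The concern holds as one of measurement. All four actions carry a recording request in one arm only, the all-four outcome comes mainly from records, and the clause that might have helped covers one item and is contradicted elsewhere in the article. The direction of the bias is clear from the text; its size is not. Under equal care, 9 practices of 30 per arm and the plan's ICC of 0.05, the scenarios shown run from about 5% (hardly above nominal) to 76%. They depend on the assumed recording rates, the assumed true rate and how strongly recording is correlated across items. A significant primary result would therefore support a claim about recorded adherence. It would not by itself establish that patients received different care.

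**What to change.** Trial status reports that the interventions have been delivered, so the changes lie in outcome definition, analysis and wording.

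1. Reconcile the abstract, Primary outcome and Data collection. Score item 3 by one definition that can be met in both arms and does not count use of the intervention checklist. State one data source for the primary outcome that applies equally to both arms.
2. Pre-specify the four-item adherence score from the already planned patient questionnaire or interview as a key secondary outcome, analysed with the same two-level model and reported with its confidence interval.
3. Word the primary conclusion as recorded adherence unless the patient-reported estimate and its interval support a change in care received. Agreement in direction alone is too weak: with no true effect, an unbiased comparison points the right way about half the time.

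**Cost.** Text changes and a mapping of questionnaire items to the four recommendations, with no new data source. Patient reports cover responders only and carry recall error. They may also be imprecise: the Patients section under Eligibility criteria invites 80 patients at follow-up without saying whether that is per practice. If it is the total, the plan's 58% response gives 80·0.58 = 46 responders, or 46/18 = 2.6 per practice; if per practice, about 46 in each. That number should be stated.
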